# Full versus half dose of antenatal betamethasone to prevent severe neonatal respiratory distress syndrome associated with preterm birth: study protocol for a randomised, multicenter, double blind, placebo-controlled, non-inferiority trial (BETADOSE)

**DOI:** 10.1186/s12884-019-2206-x

**Published:** 2019-02-12

**Keywords:** Antenatal betamethasone, Antenatal corticosteroids, Preterm delivery, Preterm birth, Respiratory distress syndrome, Non-inferiority

## Abstract

**Background:**

Although antenatal betamethasone is recommended worldwide for women at risk of preterm delivery, concerns persist regarding the long-term effects associated with this treatment. Indeed, adverse events, mainly dose-related, have been reported. The current recommended dose of antenatal betamethasone directly derives from sheep experiments performed in the late 60’s and has not been challenged in 45 years. Therefore, randomized trials evaluating novel dose regimens are urgently needed.

**Methods:**

A randomised, double blind, placebo-controlled, non-inferiority trial will be performed in 37 French level 3 maternity units. Women with a singleton pregnancy at risk of preterm delivery before 32 weeks of gestation having already received a first 11.4 mg injection of betamethasone will be randomised to receive either a second injection of 11.4 mg betamethasone (full dose arm) or placebo (half dose arm) administered intramuscularly 24 h after the first injection. The primary binary outcome will be the occurrence of severe respiratory distress syndrome (RDS), defined as the need for exogenous intra-tracheal surfactant in the first 48 h of life. Considering that 20% of the pregnant women receiving the full dose regimen would have a neonate with severe RDS, 1571 patients in each treatment group are required to show that the half dose regimen is not inferior to the full dose, that is the difference in severe RDS rate do not exceed 4% (corresponding to a Relative Risk of 20%), with a 1-sided 2.5% type-1 error and a 80% power. Interim analyses will be done after every 300 neonates who reach the primary outcome on the basis of intention-to-treat, using a group-sequential non-inferiority design.

**Discussion:**

If the 50% reduced antenatal betamethasone dose is shown to be non-inferior to the full dose to prevent severe RDS associated with preterm birth, then it should be used consistently in women at risk of preterm delivery and would be of great importance to their children.

**Trial registration:**

ClinicalTrials.gov identifier: NCT 02897076 (registration date 09/13/2016).

**Electronic supplementary material:**

The online version of this article (10.1186/s12884-019-2206-x) contains supplementary material, which is available to authorized users.

## Background

### Benefits of antenatal corticosteroids

The beneficial pulmonary effects of antenatal corticosteroids (ACS) were originally discovered in sheep in the late 60’s when Liggins noticed the partial aeration of the lungs of preterm lambs born after ACS therapy [1]. In the first randomised trial evaluating the maternal administration of corticosteroids to induce surfactant protein synthesis and accelerate fetal lung maturity in preterm neonates, Liggins and Howie showed, in comparison with placebo, lower rates of respiratory distress syndrome (RDS) in newborns whose mothers had received 2 injections of 12 mg betamethasone 24 h apart [2], a dose directly extrapolated from their sheep studies. Since then, these results have been confirmed in many trials, with no change in or even further exploration of the best regimen to use. In a meta-analysis published in 1995, it was shown that ACS administration was not only beneficial to the lungs but also to the brain and intestinal tract of preterm infants [3]. ACS therapy was consequently adopted worldwide to prevent neonatal complications associated with preterm birth [4–7]. The latest meta-analysis by the Cochrane collaboration in 2017 demonstrated that a single course of ACS in singleton pregnancies at risk for preterm delivery was associated with a 38% reduction in RDS, a 48% reduction in intraventricular hemorrhage (IVH), and a 50% reduction in necrotizing enterocolitis (NEC), resulting in an overall 25% reduction in neonatal deaths [8].

### Concerns about antenatal corticosteroids

Despite short-term benefits, concerns persist regarding the long-term effects associated with ACS. Indeed, extensive animal studies have simultaneously revealed the impact of ACS on the programming of many fetal tissues and organs [9–11]. Across species, ACS administration results in alterations of the hypothalamic-pituitary-adrenal axis [12–17], in abnormal metabolism [16, 18, 19], in hypertension [16, 20], and in delayed myelination within the central nervous system [21–23]. In humans, because most clinical trials were performed in the 70’s, 80’s and early 90’s, before early childhood assessment of perinatal interventions became standard of good research practices, long term consequences of a single course of ACS have been poorly investigated. While neurodevelopmental adverse consequences have not been reported in children, some evidence exists regarding the interaction between betamethasone and brain maturation in rodents [24, 25], suggesting that lowering the dose of antenatal betamethasone may be less detrimental for the developing brain. Finally, a trend toward insulin resistance at 30 years of age has also been reported [26].

### Dose-related effects of antenatal corticosteroids

Furthermore, results from animal and human studies have shown that these side-effects could be dose-related. Indeed, studies in sheep [27], rabbits [28], mice [29] and rhesus monkeys [30] have demonstrated that repeated ACS courses were associated with alterations in fetal growth, findings confirmed in several large retrospective human studies [31–34] and in randomised trials comparing single and multiple courses [35–39]. Similarly, a trend toward increased rates of cerebral palsy has been reported at 2 years of age in children born after 34 weeks of gestation who received four or more full courses of betamethasone [40], but not half courses [41]. In a subgroup of children finally born at term, repeated antenatal betamethasone was associated with increased rates of neurosensory disabilities at 5 years [42]. Conversely, follow-up studies comparing single and multiple courses of betamethasone at 5 and 6–8 years of age have not shown differences in the rates of severe disabilities [43, 44] or in body composition, insulin sensitivity, ambulatory blood pressure or renal function [43, 44]. These results suggest that the long-term impact of ACS is probably underexplored and possibly underestimated.

### Dose reduction of antenatal corticosteroids

Clinical trials testing dose regimens other than 12 mg betamethasone twice 24 h apart have never been performed. However, sheep studies indicate that a 50% dose reduction is as effective to induce lung maturation as a full dose [45, 46]. In this context, because dosing of ACS has not been questioned in clinical trials for more than 40 years, the Cochrane collaboration concluded that evaluation of novel antenatal corticosteroid regimens was urgently needed [47].

### Aims of the trial

The primary aim of this non-inferiority 1:1 randomised trial is to determine whether a 50% reduction of the antenatal betamethasone dose given to women at risk of very preterm delivery is not inferior to a full dose to prevent severe RDS associated with preterm birth. We made the alternative hypothesis that the difference in failure rate between the reduced-dose and the full-dose arm does not exceed 4% (corresponding to a Relative Risk of 1.20).

The secondary aims are to compare other neonatal complications between the 50% reduced and the full antenatal betamethasone dose regimen.

## Methods/design

### Study design

Randomised, multicenter, double blind, placebo-controlled, group-sequential non-inferiority trial. The trial protocol (v 5.0, November 2018) adhered to the Standard Protocol Items: Recommendations for Interventional Trials (SPIRIT) 2013 Statement for protocols of clinical trials [48].

### Setting

Thirty-seven French level 3 maternity units will be involved (Additional file 1).

### Inclusion criteria

Women are eligible for the trial if they fulfill the all following criteria:Age ≥ 18 yearsSingleton pregnancyFirst betamethasone injection already performedGestational age < 32 weeks at first betamethasone injectionInformed consent form has been obtained by the investigating obstetrician or mid-wife

### Exclusion criteria

Women are not eligible for the trial if they fulfill one of the following criteria:They had already received a full course of betamethasone.The first injection has been given by the intravascular routeIn case of preterm labor:○ Cervical dilatation at or greater than 4 cm, or○ Ultrasonographic cervical length at or greater than 20 mmAny chromosomal aberrations and/or major fetal malformationsPoor understanding of the French language

### Study interventions

Women of the standard full dose group will receive a second intramuscular injection of 11.4 mg of betamethasone (Celestene Chronodose, MSD France) 24 h after the first injection of betamethasone.

Women of the experimental half dose group will receive a second intramuscular injection of serum saline 24 h after the first injection of betamethasone.

Women of both groups justifying a rescue course of ACS are allocated a “rescue course treatment pack” from the same treatment group. All others concomitant care and interventions are permitted during the trial and none are prohibited.

### Study procedures (Fig. 1)

#### Recruitment

The trial information sheet is given to all eligible women after the first injection of betamethasone. They will be counseled by a member of the research team and encouraged to discuss the study with their family in the 24 h interval between the 2 injections and before the written informed signed consent is sought.

**Fig. 1 Fig1:**
[figure not shown]
Flow chart of the trial

#### Allocation of treatment and blinding

After obtaining maternal consent, randomisation is performed just before the second injection, using a web-based application and a secured access, in a one-to-one ratio to the full or half dose groups according to a computer-generated list of randomly permuted blocks. The randomisation is stratified by maternity units and gestational age (before or after 28 weeks). The randomisation list is centrally computer-generated and a web-based application ensures proper allocation concealment. The allocation sequence is not available to any member of the research team until the database will be completed and locked. Patients, care providers and outcome assessors are masked to assignment. A study number is allocated to the woman corresponding to a treatment pack, each of which looks identical and contains two opaque study-labeled vials.

#### Unblinding procedures

Unblinding will be requested for any reason considered essential by the investigating doctor by calling upon:the DRCD in a situation other than an emergency during the work day and during working hours, addressed to the DRCD’s project referent.the poison centre of Fernand Widal Hospital, in the case of an emergency (see emergency situations requiring unblinding), on weekends, bank holidays, when the DRCD is closed and when unblinding cannot be carried out at the DRCD

#### Women follow-up

Women will be followed from randomisation to delivery.

#### Neonatal follow-up

Follow-up visit on Day1, 48 h after birth, Day2 to Day7, and Day28 will be performed by the neonatologists in the neonatology units for preterm neonates and on Day 1 and 48 h after birth by neonatologists in the postpartum units for full term neonates. During these visits, neonatologists will assess vital and ventilation parameters of the newborns, the primary and secondary outcome measures. The last research visit will take place in the postpartum units the day of hospital discharge for full term neonates and in the neonatology units not after 37 weeks of postmenstrual age (PMA) for neonates born preterm. At this visit, secondary outcome measures will be assessed by the neonatologists.

#### Long-term children follow-up

Neurodevelopmental assessment of children by certified neuropsychologists is planned at 3 years of age, but is not part of the present protocol.

### Outcome measures

#### Primary outcome measure

The primary assessment criterion is severe respiratory distress syndrome (RDS), defined as need for exogenous intra-tracheal surfactant within the first 48 h of life. It is considered as a binary endpoint: failure in case of severe RDS, or not failure.

#### Secondary outcome measures

The secondary assessment criteria will be measured during the neonatal period until hospital discharge for children born at term and not later than 37 weeks of PMA for the premature babies. They will include:Respiratory distress syndrome defined within the first 72 h as the use of continuous positive airway pressure and/or supplemental oxygen during at least 24 h, or the use of mechanical ventilation.Transient tachypnea of the newborn defined as a need for continuous positive airway pressure and/or supplemental oxygen, resolving within 24 h.Outcomes related to the severity of RDS:○ Highest appropriate fractional inspired oxygen (FiO2),○ Maximum appropriate Mean Airway Pressure (MAP),○ Use and duration of mechanical ventilation,○ Use and duration of oxygen therapy,○ Need for oxygen therapy after 36 weeks post conception.Outcomes related to betamethasone impact on other prematurity-induced complications:○ Neonatal death before discharge*,○ Admission to neonatal intensive care unit,○ Use of inotropic support including dopamine, epinephrine, dobutamine, and norepinephrine,○ Pneumothorax,○ Patent ductus arteriosus requiring either medical or surgical treatment,○ Bronchopulmonary dysplasia at 36 weeks of PMA (need for continuous positive airway pressure or supplemental oxygen, or mechanical ventilation),○ NEC and grade according to Bell classification [49],*○ IVH and grade according to the Papile classification [50],*○ Cystic periventricular leukomalacia,○ Use of postnatal steroids (either inhaled or systemic),○ Retinopathy of prematurity requiring anti-VEGF treatment or laser*,○ Length of hospital stay before the first discharge home,○ Survival without severe RDS, IVH grade 3 and 4, NEC grade ≥ 2, or retinopathy of prematurity treated by anti-VEGF or laser.Outcomes related to potential adverse events of betamethasone○ Birth weight at birth,○ Head circumference at birth,○ Body length at birth,○ Suspected or confirmed early onset sepsis treated using antibiotics during 7 days,○ Hypoglycaemia requiring oral or IV glucose administration or glucagon within 7 days.

Outcomes marked with an asterisk * are the four *safety outcomes* that will be monitored at each interim analysis.

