#### Interim analysis

To address the ethical concerns of (i) studying a high-risk population (pregnant women and preterm neonates), (ii) the potential increased rates of babies with severe RDS due to the reduction of the betamethasone dose, (iii) the anticipated length of time of inclusion (30 months), (iv) the number of infants planned for a fixed analysis (*n* = 3142) and (v) the primary endpoint measured in the first 48 h of life, a sequential data analysis method will be used, allowing to provide stopping rules. Analyses will be done after every 300 neonates who reach the primary outcome on the basis of intention to treat. The trial may be stopped for the following reasons:i.Inferiority of the experimental group on the primary outcome,ii.Non-inferiority of the experimental group on the primary outcome,

Finally, a maximum of 11 analyses is planned.

For the primary outcome, a non-inferiority sequential design with alpha and beta spending functions will be used to control the first type and second type error, respectively. For the estimation of the boundary curves, we chose a monotone function proposed by *Kim and DeMets* and generalized by *Jennison and Turnbull* [55, 56]. Critical values of the boundary curves are defined for each interim analysis. At each interim analysis, the maximum likelihood estimator of the difference of treatment failure rates between full-dose and half-dose will be compared to these critical values and the necessity to stop the trial will be checked.

In addition to that sequential primary analysis, the rate and percentage of the four safety outcomes (marked above with an *: neonatal death, IVH grade 3 and 4, NEC grade ≥ 2, and retinopathy of prematurity treated by anti-VEGF or laser) will be estimated in order to detect a potential increasing in the experimental group. Those estimation will be made on the overall population, and by gestational age at birth (born before 28 weeks, between 28 and 32 weeks, and after 32 weeks), as expected prevalence are different from one subgroup to the other.

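### Assessment of preterm infants ends by 37 weeks PMA, but length of stay (and, read literally, death) is defined to discharge

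*Protocol article*

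**What the plan says.** Two sections of the protocol article set the same limit. Under Secondary outcome measures, the criteria are measured "until hospital discharge for children born at term and not later than 37 weeks of PMA for the premature babies". Under Neonatal follow-up, the last research visit takes place on "the day of hospital discharge for full term neonates", but "in the neonatology units not after 37 weeks of postmenstrual age (PMA) for neonates born preterm". Only term infants are followed to discharge.

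The list under Secondary outcome measures nevertheless contains, with no distinction by gestational age, "Length of hospital stay before the first discharge home" and "Neonatal death before discharge". The second is one of four monitored safety outcomes. Treated retinopathy is another, and its definition names neither discharge nor an age.

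For monitoring, the Interim analysis section states: "Analyses will be done after every 300 neonates who reach the primary outcome on the basis of intention to treat". It gives as one reason for a sequential design "the primary endpoint measured in the first 48 h of life". At each look "the rate and percentage of the four safety outcomes" is estimated overall and by gestational age at birth. No condition on completed follow-up is given.

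**The concern.** An outcome that runs to discharge cannot be completed in an infant whose assessment ends before discharge. Preterm infants still in hospital at 37 weeks PMA have the longest stays, so the cut falls on the part of the distribution where stays could differ most. The Final analyses section compares continuous outcomes by Student or Mann-Whitney-Wilcoxon tests, and neither allows for censoring. Depending on how these infants are handled, their stay is shortened or they drop out of the comparison.

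The same limit may leave out late in-hospital deaths, depending on what the death outcome means. It also sets a short horizon for treated retinopathy, which feeds the survival composite as well as the safety monitoring.

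A second, weaker issue is interim maturity. The looks are timed by a 48-hour outcome, while the four safety outcomes can take weeks to emerge.

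**Working it through.** **1. Length of stay.** An infant born at gestational age g can contribute at most 37 − g weeks of observed stay:
- born at 24 weeks: 13 weeks (91 days)
- born at 26 weeks: 11 weeks (77 days)
- born at 28 weeks: 9 weeks (63 days)
- born at 32 weeks: 5 weeks (35 days)

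As an illustration, an infant born at 26 weeks and discharged at 40 weeks PMA stays 98 days, of which at most 77 lie inside the window. This does not depend on how any other outcome is read.

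**2. Death.** Day 28 falls at g + 4 weeks PMA, and g + 4 < 37 when g < 33. If neonatal means the first 28 days, every birth before 33 weeks is covered, and Neonatal follow-up schedules a Day 28 visit. If the outcome means any death before discharge, a death after 37 weeks PMA in a preterm infant still in hospital lies outside the window. The article does not choose between these readings. By the same arithmetic, Day 28 for a preterm birth at 34 weeks falls at 38 weeks PMA, after the limit for the last visit.

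**3. Infants with a truncated window.** From the Sample size and Interim analysis sections, 33% of 3,142 deliver before 32 weeks: 0.33 × 3,142 ≈ 1,037. The share still in hospital at 37 weeks PMA is not given. Assuming 15–40%: 0.15 × 1,037 ≈ 155 and 0.40 × 1,037 ≈ 415.

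**4. What triggers a look.** The plan's maximum of 11 analyses reproduces if 300 counts infants assessed: 3,142 / 300 = 10.47, rounded up to 11. So a look follows 300 infants with a known 48-hour outcome, not 300 failures. The sample size also reproduces (2 × 0.20 × 0.80 × (1.960 + 0.842)² / 0.04² ≈ 1,570 per group, against 1,571) and is not at issue.

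**5. Maturity at the looks.** With 3,142 births spread evenly over the stated 30 months (about 130.4 weeks), there are 24.1 births a week, so 300 take about 12.5 weeks. At look k, the share of infants born at g who have not reached 37 weeks PMA is min(1, (37 − g) × 24.1 / (300k)). Averaged over births before 32 weeks, assuming birth ages spread evenly over 24–32 weeks:

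| Look | Not yet at 37 weeks PMA | Range if inclusion takes 48 to 24 months |
|---|---|---|
| 1 | 72% | 45–85% |
| 2 | 36% | 23–45% |
| 5 | 14% | 9–18% |
| 10 | 7% | 4.5–9% |

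A simulation that starts from enrolment gives a lower figure at look 1. It assumes 70–105 women a month, gestational age at randomisation uniform over 24–32 weeks, 33% delivering before 32 weeks after a short latency, and the rest delivering around 36.5 weeks. There, 54–67% of births before 32 weeks have reached 37 weeks PMA at look 1, so 33–46% have not; at look 2, 19–27% have not. With mean latency set at 1–2 weeks, the look 1 figure is 31–45%. Across the two models, with inclusion at the planned pace, roughly 30–70% are unfinished at look 1, and under about 10% by look 10.

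**The case against.** The strongest reply is that only length of stay is a plain contradiction, and it is not a safety outcome. Much of this stands.

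- **Death.** The listed outcome carries the word neonatal, and the Interim analysis section calls it simply neonatal death. On a 28-day reading nothing is lost in the high-risk group. A reader might infer that deaths before discharge cannot be observed in the sickest infants; the text supports only an ambiguity.
- **Retinopathy.** Its definition does not run to discharge, so the 37-week limit is a common horizon in both arms. It is therefore not shown that two of the four safety outcomes are incomplete against their own definitions.
- **Interim rates.** A reader might infer that infants aged 48 hours are counted as event-free. The article does not say so. The overall population is named in contrast to the gestational-age groups, and the denominator may be fixed in a statistical plan or DSMB charter that is not shown; the Ethics section says a statistical plan was approved by the DSMB.
- **Direction.** Immaturity should be similar in two blinded 1:1 arms, so it lowers both rates and the information without a shown bias towards half dose. It fades at later looks. Under Safety monitoring, the DSMB also receives all adverse events and further analyses can be requested.
- **Size.** The 15–40% share has no source in the article, and a truncated window is not a lost event.

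The reply does not remove the conflict itself. The 37-week limit is stated twice, so it is not a detail left out by condensing, and a stay that runs to discharge home does not fit inside it.

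**Conclusion.** The concern holds in a limited form. Followed as written, the plan truncates length of stay for every preterm infant still in hospital at 37 weeks PMA, and the planned tests do not allow for it. Whether deaths are also missed depends on an undefined term. For retinopathy, the limit is a short horizon for a monitored safety outcome. The number of infants affected cannot be derived from the article; 155–415 rests on the assumed 15–40% and counts truncated windows only.

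The interim point is secondary and held with lower confidence. Early safety rates may include many infants with unfinished follow-up, but the figures rest on assumed accrual and birth ages, and an unshown document may already set the denominator. The sample size and primary outcome are unaffected.

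**What to change.** Reconcile the Neonatal follow-up and Secondary outcome measures sections in one of two ways.

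1. **Preferred.** For every infant, collect date of first discharge home, vital status and retinopathy treatment to first discharge home. Keep 37 weeks PMA only for outcomes fixed at that age. State whether neonatal death means 28 days or any death before discharge.
2. **Otherwise.** Redefine these outcomes as running to 37 weeks PMA, and analyse stay as censored at that age.

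The first option adds some eCRF fields and record abstraction, including after transfers, and a slightly later data lock. The research technicians who already collect follow-up could do this. The second needs no new data, but gives up the later part of stay and any later events.

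For the looks, unless an existing document already does so, report the four safety rates on infants who have completed the outcome window or died. List the rest as pending, with events to date. This changes the layout of the DSMB report only; the timing of looks and the boundaries stay as they are.

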### Statistical analysis

#### Sample size

To study the non-inferiority of the 50% reduced betamethasone dose regimen, we will test the alternative hypothesis that the difference in failure rate between the half-dose and the full-dose arm do not exceed 4% (corresponding to a Relative Risk of 1.20). This non-inferiority margin has been obtained through a consensus between the investigators of the GROG, neonatologists and the methodologists of the study, considering that a 4% difference is the smallest value that would be clinically relevant between arms and correspond to the preservation of a 70% of the effects of the full dose betamethasone regimen over placebo. Indeed, in the French Epipage2 study (2011) [51], 62% of the neonates exposed to antenatal betamethasone and born before 32 weeks of gestation from a singleton pregnancy received exogenous surfactant. Assuming that 33% (conservative hypothesis) of the randomised women will indeed deliver before 32 weeks, we estimated that 20% of the included pregnant women receiving the full betamethasone dose regimen would have a neonate with severe RDS, defined as the need for exogenous intra-tracheal surfactant. According to the literature, ACS is responsible for an average relative risk of RDS of 0.66 (95% CI 0.56 to 0.77), compared to placebo [8, 52]. Assuming a prevalence of severe RDS of 20% in the full dose betamethasone regimen, to preserve 67% of the upper bound for the historical difference between full dose and placebo (i.e. 0.67 x (0.20–0.20/0.77)) gave a margin of 4% (or expressed as Relative Risk (20 + 4) / 20 = 1.20). Thus, 1571 patients in each treatment group are required to test the non-inferiority hypothesis, with a 1-sided type-1 error of 0.025, a power of 0.80, and a non-inferiority margin equal to 4% [53].

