#### Final analyses

Data analysis and reporting will follow the CONSORT guidelines for non-inferiority randomised controlled trials [57]. The two groups will be compared for women’s and neonate’s characteristics. Qualitative variables will be summarised by numbers and percentages of patients in each treatment group.

The final primary non-inferiority statistical analysis will be conducted on all the neonates enrolled in the trial, including those who did not participate in the interim analysis. The difference between the failure rates observed in both arms along with its 2-sided confidence interval will be estimated. The final boundary for difference will be compared to the critical value corresponding to the number of women finally included, to claim or not the non-inferiority. A figure showing confidence intervals and the margin of non-inferiority will be used to summarize the result on the primary outcome.

The analyses on the other pre-specified secondary outcomes will consist in estimations and comparisons between the two arms. The 95% confidence interval for the difference between arms will be constructed. The χ2 or Fisher’s exact test for categorical variables and Student or Mann-Whitney-Wilcoxon test for continuous variables will be used to compare the full-dose and the half-dose regimens, according to the validity conditions. All these statistical tests will be two-sided and the level of statistical significance will be set at 5% (2-sided).

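### Birth weight, head circumference and length are compared without standardising for gestational age at birth, which is valid but imprecise when births run from very preterm to term

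*Protocol article*

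**What the plan says.** In the protocol article, Secondary outcome measures places birth size under the group "Outcomes related to potential adverse events of betamethasone" and defines it as "Birth weight at birth,○ Head circumference at birth,○ Body length at birth". No z-score, centile or small-for-gestational-age form is named.

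Final analyses states the method for continuous secondary outcomes: "Student or Mann-Whitney-Wilcoxon test for continuous variables will be used to compare the full-dose and the half-dose regimens", two-sided at 5%, with a 95% confidence interval for the difference. No covariate is named.

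Four other sections matter here:

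- **Spread of births.** Women enter if the first injection was given before 32 weeks (Inclusion criteria). Sample size then reads "Assuming that 33% (conservative hypothesis) of the randomised women will indeed deliver before 32 weeks", which leaves about 67% delivering later. Neonatal follow-up provides for visits "on Day 1 and 48 h after birth by neonatologists in the postpartum units for full term neonates".
- **Stratification.** Allocation of treatment and blinding stratifies by unit and by gestational age before or after 28 weeks. That is age at randomisation, not at birth.
- **Subgroups.** Subgroup analyses splits by gestational age at birth and by the newborn's sex. It repeats only the primary outcome, death, the named complications and the composite. Birth size is not among them.
- **Rationale.** Dose-related effects of antenatal corticosteroids reports that "repeated ACS courses were associated with alterations in fetal growth".

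**The concern.** Birth size is in the outcome list to show whether the dose affects fetal growth. In a population born from very preterm to term, most of the variation in weight, head circumference and length comes from the age at which the infant was born, not from growth at a given age. An unadjusted comparison carries all of that variation in its standard error.

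Long-term neurodevelopment lies outside this protocol (Long-term children follow-up). Birth size is therefore one of the few outcomes here that could show an advantage of the lower dose. If the comparison is too imprecise to see a modest growth difference, a non-significant result may be read as evidence that halving the dose makes no difference to growth. The data could not support that reading.

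**Working it through.** **1. The plan's own figure.** With a 20% failure rate in both arms, a margin of 4%, one-sided 0.025 and power 0.80:

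n per arm = (1.960 + 0.842)² × 2 × 0.20 × 0.80 / 0.04² ≈ 1570

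The article states 1571, so the figure reproduces. I use 1571 per arm below. The article gives no standard deviation, effect size or power for the growth outcomes.

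**2. Assumptions for birth weight (none is in the article except the 33%).**

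- 33% of births spread evenly over 25-32 weeks and 67% evenly over 32-41 weeks.
- Mean weight 800 g at 25 weeks, rising 150, 180 or 200 g per week.
- Within-age coefficient of variation 12% or 15%.

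**3. Formulas.**

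- Detectable difference at 80% power, two-sided 5%: (1.960 + 0.842) × SD × √(2/1571) = 0.100 × SD.
- Share of variance due to gestational age: 1 − (within-age SD / raw SD)².
- Sample-size ratio for equal precision: (raw SD / within-age SD)².

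**4. Results from simulating that mixture.**

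| Rise per week, CV | Raw SD (g) | Within-age SD (g) | Share due to age | Detectable, raw (g) | Detectable, within age (g) | Sample-size ratio |
|---|---|---|---|---|---|---|
| 150 g, 12% | 723 | 268 | 0.86 | 72 | 27 | 7.3 |
| 150 g, 15% | 750 | 335 | 0.80 | 75 | 33 | 5.0 |
| 180 g, 12% | 860 | 303 | 0.88 | 86 | 30 | 8.0 |
| 180 g, 15% | 889 | 379 | 0.82 | 89 | 38 | 5.5 |
| 200 g, 12% | 953 | 327 | 0.88 | 95 | 33 | 8.5 |
| 200 g, 15% | 984 | 408 | 0.83 | 98 | 41 | 5.8 |

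**5. Power for a true difference of 50 g.** This effect is illustrative; the article names none. Power = Φ(50 / (SD × √(2/1571)) − 1.960), with √(2/1571) = 0.0357.

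- Raw, SD 723 g: 50/25.8 = 1.94, power 49%.
- Raw, SD 984 g: 50/35.1 = 1.42, power 30%.
- Within age, SD 408 g: 50/14.6 = 3.43, power 93%.
- Within age, SD 268 g: 50/9.56 = 5.23, power over 99%.

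**6. Sensitivity to the spread of later births.** If births after 32 weeks cluster towards term, the raw SD is 782-1065 g and the within-age SD 287-441 g. The detectable differences become 78-106 g and 29-44 g, and the sample-size ratio 5.1-8.6. Power for 50 g becomes about 26-43% raw against 89% or more within age.

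**7. Early stopping.** Interim analysis allows a look after every 300 neonates, about 150 per arm. The multiplier is then 2.802 × √(2/150) = 0.3235. Using the SDs in step 4, the detectable difference would be about 234-318 g raw (0.3235 × 723 to 0.3235 × 984) against 87-132 g within age (0.3235 × 268 to 0.3235 × 408).

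**8. On the z-score scale**, with an assumed SD of 1, the detectable difference at 1571 per arm is 0.10 SD.

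Only birth weight was calculated. Head circumference and length also increase with gestational age, so the direction is the same, but the size was not computed.

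**The case against.** **The scale may be settled elsewhere.** The article gives no units, and a t-test on z-scores would fit its wording. The Ethics section says a statistical plan was written before the trial began; it is not shown here. This limits the point but does not remove it. The article names the measurements themselves and an unadjusted test, and its analyses by gestational age at birth leave growth out. If the full plan already standardises, the change reduces to aligning the article's definition with it.

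**The comparison is not biased.** A reader might infer that a chance difference in delivery timing would be mistaken for a growth effect. The documents do not support treating that as a separate flaw. Randomisation balances gestational age at birth in expectation, apart from any effect of the dose on timing, which belongs to the unconditional contrast. Chance imbalance is already inside the planned test and confidence interval. The loss is one of precision.

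**Growth is not the whole rationale.** A reader might also infer that growth is the main harm behind the trial. The Background gives it as one dose-related concern, with neurodevelopmental and metabolic ones, and the growth evidence it cites concerns repeated courses.

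**The size rests on outside assumptions.** This stands. A power contrast computed at 0.10 SD would be circular, because that is the effect for which z-scores have 80% power by construction. The 50 g figure avoids this but is itself only illustrative. Growth-restricted pregnancies are not excluded, so the spread of z-scores could exceed 1, and the detectable difference would grow in proportion.

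**Standardising changes the question.** Gestational age at birth is measured after randomisation, so a z-score comparison conditions on something treatment could affect. This stands, and it is why the raw comparison must be kept alongside.

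**Conclusion.** The point holds as a loss of precision in three secondary outcomes. As the article defines them, the birth-size comparisons are valid, but under the assumed growth curves they would need about 5 to 9 times as many infants as a comparison within gestational age for the same precision. At full size, raw birth-weight differences above roughly 72-98 g (up to 106 g under the alternative spread of births) would still be detectable with 80% power. Smaller ones would often be missed. A non-significant raw difference would therefore be weak evidence about fetal growth.

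The direction depends only on births running from very preterm to term, which the article states. The size depends on assumed weights and standard deviations that it does not give. The primary non-inferiority conclusion, the stopping rules and the four monitored safety outcomes are untouched.

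**What to change.** Define the three outcomes as z-scores for gestational age at birth and sex on one reference chart, named in advance. Compare mean z-scores between arms with a 95% confidence interval. Add birth weight below the 10th centile on the same chart as the binary form.

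Report the raw comparison and the distribution of gestational age at birth by arm beside these results, so that a reader can see whether delivery timing differs between arms.

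The cost is wording in Secondary outcome measures and Final analyses, plus the choice of chart, settled before unblinding. No new data are needed, because gestational age at birth and the newborn's sex already define the planned subgroups. The remaining drawback is the conditioning on a variable measured after randomisation, and the parallel raw report makes that visible.
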